### Study objectives and research hypotheses

The primary objective of this pilot study is to examine the acceptability and feasibility of i) the study design; ii) the experimental nursing intervention; and iii) a novel measure, cerebral _r_SO_2_ obtained by NIRS, a non-invasive method to detect cerebral oxygen imbalances among patients with delirium as well as its validity among patients with delirium.

The secondary objective of this pilot study is to examine the preliminary effect of the intervention on patient and caregiver outcomes. The following are the research hypotheses for the study’s secondary objective:

For patient outcomes

Compared with controls, patients in the intervention group will present:

Less severe delirium in the 3 days following onset;Fewer complications (defined as either a sternal wound dehiscence, fall, respiratory tract infection, or accidental removal of urinary catheter, drain, arterial line or endotracheal tube) in the 3 days following onset of delirium;Shorter total length of ICU and total hospital stay;Enhanced psycho-functional recovery one month after the onset of delirium;

For caregiver outcomes

In comparison with controls, caregivers in the intervention group will present:

(H5)A lower anxiety level after the intervention (Day 4 following delirium onset), at Day 15, and at 1 month following delirium onset;(H6)A higher sense of self-efficacy after the intervention (Day 4 following delirium onset), at Day 15, and at 1 month following delirium onset.

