### Data collection and analysis

#### Statistical methods

The planned analyses concerning all the primary objectives include descriptive statistics, which, along with 95% CI, will be used to portray the intervention and study design’s acceptability and feasibility criteria. Control and experimental group descriptions will be achieved using descriptive statistics reflected by n, mean, standard deviation, and median, minimum, and maximum for continuous variables and frequencies and percentages for categorical variables; 95% CIs will also be presented when appropriate. Finally, to evaluate the validity of cerebral _r_SO_2_, a Pearson or Spearman correlation will be used (depending on level of measurement) to correlate oximetry scores and scores obtained on the ICDSC, DI, and CAM-ICU at Days 1, 2, and 3 following the onset of delirium.

The planned analyses for the study’s secondary objective of preliminary efficacy will include the statistical methods detailed below. It should first be noted that this is a pilot study assessing the feasibility of a larger study and statistical analyses will be used to examine the preliminary effects of the intervention and determine any trend in the results as this study is not powered for statistical testing. For H1 relative to delirium severity, a repeated measure ANCOVA will be performed using the DI scores taken on Days 1, 2, and 3 following delirium onset. The initial scores on the ICDSC taken at delirium onset will be used as a covariate. Post-hoc tests will be performed if the omnibus test is significant for the group by time interaction. Such an interaction would imply that delirium severity is different between groups over the three days. Mixed models will be used so that a patient with missing data at Days 1, 2, and 3 following the onset of delirium will not be excluded from the analysis. The intent-to-treat principle will be respected; all the patients in the study will be included in the analysis according to their group of randomization. Because the pilot study will not be used to definitely assess the efficacy of the intervention (this would be the objective of the larger study), we plan to conduct a sensitivity analysis using the last observation carried forward.

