For hypothesis H2 on adverse clinical complications following onset of delirium, a combined outcome measure will be used (mention in the hospital chart of sternal wound dehiscence, a fall, respiratory tract infection, or accidental removal of urinary catheter, drain, arterial line or endotracheal tube = yes/no) and groups will be compared using a χ^2^ test.

Student’s T-tests for independent groups will be used for hypothesis involving continuous variables H3 on length of ICU and total hospital stay, H4 on psycho-functional recovery 1 month after the onset of delirium, H5 on caregiver’s anxiety level, and H6 relative to caregiver’s sense of self-efficacy. The planned treatment for missing data for hypotheses H3 to H6 is assigning the value corresponding to the group mean.

Assumptions underlying the planned models will be checked and alternative methods may be used if more appropriate. A significance level of 0.05 will be used for all analyses.

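### H5 and H6 predict a difference at three time points but are analysed only by t-tests at 0.05, with no rule on which result decides

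*Protocol article*

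**What the plan says.** Under Study objectives and research hypotheses, H5 reads "A lower anxiety level after the intervention (Day 4 following delirium onset), at Day 15, and at 1 month following delirium onset". H6 has the same form: "A higher sense of self-efficacy after the intervention (Day 4 following delirium onset), at Day 15, and at 1 month following delirium onset". Table 1 confirms the schedule: both scales are completed at enrolment and then at Day 4, Day 15 and Day 30.

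Under Statistical methods, one method covers H3 to H6. Student's "T-tests for independent groups will be used for hypothesis involving continuous variables H3 on length of ICU and total hospital stay", on H4, and then "H5 on caregiver’s anxiety level, and H6 relative to caregiver’s sense of self-efficacy". No time point, change score, average or repeated-measures contrast is named for H5 or H6. The section closes with "A significance level of 0.05 will be used for all analyses".

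The same section treats H1 (delirium severity on Days 1 to 3) differently. H1 gets a repeated-measures ANCOVA fitted as a mixed model, and "Post-hoc tests will be performed if the omnibus test is significant for the group by time interaction". The section also says that the analyses serve to look at preliminary effects and "determine any trend in the results as this study is not powered for statistical testing", and that the pilot is not meant as a definitive assessment of efficacy.

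**The concern.** An independent-groups t-test takes one value per person. Three post-baseline assessments therefore most naturally mean three tests for H5 and three for H6. The article does not say whether support requires one significant visit, a particular visit, or all three. The conjunction in the hypotheses hints at all three, but no decision rule says so. If the visits disagree, the verdict depends on a choice made after the results are seen.

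The article also says two things that do not fit together. It describes the efficacy work as a search for trends in a study not powered for testing, yet it fixes a significance threshold for every analysis and makes the H1 post-hoc tests depend on significance. At stake is whether a significance statement on H5 or H6 from this pilot has a defined meaning.

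**Working it through.** **Inputs from the article**
- Level: 0.05 for every analysis. Sidedness is not stated, so two-sided 0.05 is assumed. The hypotheses are directional ("Compared with controls, patients in the intervention group will present", with parallel wording for caregivers), so the favourable-direction rate is also shown, at 0.025 per test.
- Sample: 30 dyads. The split is not given, so 15 per group is assumed.
- Number of tests: H1 1 + H2 1 + H3 2 (ICU and hospital stay) + H4 1 + H5 3 + H6 3 = 11, before any post-hoc tests.

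**Assumed, because the article gives no figure:** correlation 0 to 0.8 between visits or outcomes, and standardized true effects of 0.5 to 1.0 SD. Participants are treated as independent and all 11 tests are approximated by t-tests.

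**The plan's own figure.** The only computed figure is the precision of the consent proportion: 1.96 × √(0.75 × 0.25 / 30) = 0.155. The stated ±15.5% reproduces. The article gives no error rate for the efficacy tests.

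**One outcome (H5 or H6), three visits, no true effect.** Under independence, any of three significant = 1 − 0.95³ = 0.143, and any favourable = 1 − 0.975³ = 0.073. With correlation, simulated 15 v 15 t-tests give:

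| Correlation | Any of 3, two-sided | Any of 3, favourable | All 3 favourable |
|---|---|---|---|
| 0 | 0.14 | 0.07 | <0.001 |
| 0.5 | 0.13 | 0.06 | 0.001 |
| 0.8 | 0.10 | 0.05 | 0.007 |

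A single test has 0.05 two-sided and 0.025 favourable. The any-visit reading thus doubles to nearly triples the error rate, and the all-visits reading cuts it to under 1%.

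**One outcome, three visits, a true effect at every visit**

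| True effect | Correlation | Any of 3 | All 3 | Some but not all |
|---|---|---|---|---|
| 0.5 SD | 0.5 | 0.48 | 0.08 | 0.41 |
| 0.5 SD | 0.7 | 0.43 | 0.11 | 0.32 |
| 0.8 SD | 0.5 | 0.81 | 0.31 | 0.50 |
| 0.8 SD | 0.7 | 0.75 | 0.37 | 0.38 |
| 1.0 SD | 0.5 | 0.93 | 0.53 | 0.40 |

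The last column is the share of trials in which the two readings give opposite verdicts.

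**All 11 tests, no true effect.** Under independence, 1 − 0.95¹¹ = 0.431 two-sided and 1 − 0.975¹¹ = 0.243 favourable. At a common correlation of 0.8, simulation gives 0.18 and 0.09.

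**Averaging three visits.** The variance relative to one visit is (1 + 2ρ)/3. At ρ = 0.5 it is 0.667, with square root 0.816, so the standard error is 18% lower. At ρ = 0.8 it is 0.867, with square root 0.931, so it is 7% lower.

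**The case against.** The strongest reply is that status already deals with this. Efficacy is the secondary objective, the results are called preliminary, and the main indicator is caregiver consent, reported descriptively with a confidence interval. A rule for time points in secondary pilot outcomes is often left to an analysis plan, and the article says that its analyses are also described in the registration form. Neither is at hand. Three separate t-tests are also an inference: a change score or mean score is not ruled out, and the article allows alternative methods.

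Much of this stands. For a pilot of this kind, unadjusted multiplicity is a minor matter. But the article did choose a test and a threshold for H5 and H6, and the choice does not match hypotheses stated at three visits. The allowance for alternative methods concerns model assumptions, not which visit decides. The not-powered caveat does not cancel a significance level imposed on every analysis.

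A reader might infer more than the documents support:
- **That a chance finding is likely.** It is not: 0.18 to 0.43 across 11 tests, and 0.09 to 0.24 if only favourable results count, always below one half.
- **That an all-visits rule is nearly impossible to meet.** The rate under 1% applies when there is no effect. With true effects of 0.5 to 1.0 SD and correlation 0.5, it is met in about 8% to 53% of trials.
- **That H5 and H6 have the same data structure as H1.** They do not. Table 1 gives them a baseline score, which the Delirium Index lacks, so the H1 model cannot simply be copied.
- **That a chance result would be picked to lead the larger trial.** No section says that p-values will choose its outcome.

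**Conclusion.** The point holds in a limited form. H5 and H6 have no deciding contrast, and the only method named, on its natural reading, yields three verdicts per outcome. Under no effect the false-positive rate in the favourable direction runs from under 1% to 0.07, depending on a rule that the plan does not state. With a true effect of 0.5 to 0.8 SD and correlation 0.5 to 0.7, the any-visit and all-visits readings disagree in about 32% to 50% of trials. These figures rest on 15 per group, two-sided 0.05 and the assumed correlations and effects. That the rule is missing rests on the text alone.

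Separately, a 0.05 level for all analyses is at odds with the article's own description of the efficacy work. It should be changed for consistency, not because a pilot needs multiplicity control. The change is worth making, but it does not touch the primary feasibility objective.

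**What to change.** Analyse H5 and H6 each with one mixed repeated-measures model over Days 4, 15 and 30, adjusted for the baseline score that Table 1 already collects. Name one summary contrast in advance, for example the group difference averaged over the three visits, and report the visit-specific differences beside it. They are needed because H5 and H6 predict a difference at each visit, and an average can look favourable when the effect has faded by Day 30. With a likelihood-based model, the planned group-mean imputation is no longer needed for these two outcomes.

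Replace the sentence that sets 0.05 for all analyses with a statement that efficacy results are reported as estimates with 95% confidence intervals and without significance claims. The significance condition on the H1 post-hoc tests should be reworded to match.

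The cost is a change of wording and two models in place of six t-tests, on data already being collected. The downside is that an isolated p<0.05 at one visit can no longer be called support for a hypothesis.

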### Ethical considerations

Institutional review board approval was obtained from the relevant hospital in January 2013 (Project number assigned by the Montreal Heart Institute Ethics committee: 2012–288, 1420). Measures to protect confidentiality of study participants were put in place; all information collected will be held securely, with an identification number assigned to each participant to protect confidentiality. Amendments to protocol will be communicated through additional information in the trial registration form on the website of http://www.controlled-trials.com. Finally, to our knowledge, the proposed intervention poses no risk to participants.

## Discussion

### Study limits

The pilot study’s aim is to assess the acceptability, feasibility, and preliminary efficacy of a nursing intervention enabling family caregivers to be involved in delirium management. The study also aims to provide evidence of the validity of cerebral _r_SO_2_ obtained by NIRS among patients with delirium. The preliminary effects will be evaluated for both patient outcomes (delirium length and severity, adverse clinical outcomes, length of ICU and hospital stays, psycho-functional recovery) as well as caregiver outcomes (anxiety and self-efficacy). This experimental nursing intervention was designed based on previous studies in the fields of delirium and dementia, as well as on clinical guidelines, and is grounded in three theoretical frameworks.

Throughout the design of this study protocol, an effort was made to reduce possible severe threats to validity identified by the Cochrane Collaboration [50]. These threats include issues related to: i) sequence generation and allocation concealment (selection bias); ii) potential threats to blinding of participants and outcomes; iii) between-group contamination (performance and detection bias); and finally iv) incomplete outcome data and selective outcome reporting (attrition and reporting bias).

In the present study, the sequence generation of the random group assignment will be carried out by experts from an independent clinical trial coordinating center (Montreal Health Innovations Coordinating Center). They will provide sealed opaque envelopes to be opened by the study nurse on the first Monday of the beginning of each 2-week block. In addition, a detailed flowchart of approached, randomized, and assigned participants will be included in the final report as well as a description of participants’ baseline characteristics.

Given the fact that blinding from group allocation is not possible for the patient, caregiver, and nurse-mentor, it is planned that all bedside nurses, medical team members, and research assistants be blinded. Nursing and medical staff will not be notified of week allocation, and the nurse-mentor will be present on the research wards during weeks allocated to both intervention and control groups. Therefore, delirium scores collected by the nurses will have been collected by professionals blinded to group assignment. The research assistant will also blinded to the study group when collecting data. The analyses will be conducted by an analyst blinded to group allocation insured by a codification of group allocation.

Another closely related potential bias is between-group contamination. This issue was addressed while planning the randomization scheme. The randomization of blocks of time followed by washout periods is designed to avoid this bias. In addition, pre- and post-visit encounters between the caregiver and the nurse-mentor will be held away from other families.

Finally, in an attempt to reduce potential issues with selective outcome reporting, all the planned feasibility and acceptability evaluation criteria as well as statistical analyses of outcomes have been described in the trial registration form (http://www.controlled-trials.com; #ISRCTN95736036).

However, despite this cautious approach in the study protocol, other threats to validity cannot be controlled. For instance, caregivers’ involvement in delirium management will result in an individualized dosage and quality of the intervention since all individuals have different resources to deal with this complex situation. To describe the intervention delivered, the caregiver’s presence and use of recommended behaviors will be closely monitored and reported; these data may also permit the exploration of the relationships between the specific types of intervention (e.g., type of caregiver behavior effectively performed, number of behaviors, number of encounters, duration of encounters) and the outcomes. These types of exploratory analysis serve to describe possible links between specific interventions and outcomes [16]. The use of only one study hospital poses another potential threat, this time to external validity. To minimize this bias, a thorough description of both the hospital setting and the type of patients will be provided. The fact that the intervention will be provided by one study nurse-mentor with an expertise in intensive care and delirium also limits the general application of the intervention by nurses with different expertise.

One last concern linked to the experimental intervention is its acceptability to caregivers and its feasibility in a context of delirium with a high variability of symptoms. A patient’s delirium is associated with high anxiety in caregivers [8–10] which could present a barrier to their involvement. Therefore, in evaluating the intervention’s acceptability, one main indicator was to obtain consent from at least 75% of the caregivers approached to participate in the study. The intervention’s feasibility will be evaluated based on the indicators presented in Table 4.

### Preliminary feasibility results

Within the first few months of the empirical phase we encountered challenges in the prediction and detection of delirium, as well as some ethical dilemmas. Because patients can show signs of delirium immediately upon waking from surgery, our original protocol mandated preoperative recruitment in order to ensure their informed consent before the surgery to participate in the study. In addition, in order to limit the number of patients approached before surgery our ethics committee suggested limiting screening to only those patients at high risk of developing delirium. Based on the available literature [4, 5, 51] and our clinical experience with delirium in the cardiac surgery population, it was hypothesized that patients with three or more of the risk factors for delirium (aged over 65, history of delirium, active smoking, consumption of at least three alcoholic beverages daily, or sensory impairment (sight, hearing)), would be more susceptible to developing post-surgical delirium. However, after a few weeks of recruitment it was evident that most delirium episodes occurred in patients with less than three risk factors (i.e., those from whom we did not have pre-operative consent), and did not necessarily occur in those with three or more. Therefore, we concluded that even though several risk factors for delirium have been identified [4, 5, 51], the surgery itself and age over 65 seem to be enough to trigger postoperative delirium in our patients. In light of this, the recruitment strategy protocol initially planned as a preoperative approach was amended with approval from the ethics committee to allow a postoperative approach, i.e., when delirium is observed after the surgery, in order to facilitate the inclusion of participants in the study.

The postoperative approach to recruitment implied specific ethical issues because patients with delirium lose their ability to give informed consent for the duration of their delirium. Given that the experimental intervention had little potential for deleterious effects, that a caregiver was involved, and that the patients would be able to consent after resolution of their delirium, the ethics committee allowed a new procedure for recruitment. This procedure included obtaining informed consent from the caregiver only during the delirium, followed by informed consent from the patient once the delirium resolved. The ethics committee’s decision was also based on a modified article of the Quebec Civil Code [52] which now allows the family to consent for the temporarily cognitively impaired parent in studies in which potential deleterious effects are minimal. This is parallel to the consent for care that can be provided by family members in clinical care settings when the ill person is unable to consent due to cognitive impairment. Therefore, in the present study, we obtain informed consent from caregivers when patients themselves are unable to consent. The patient has to consent for the study after emerging from the delirium before the time or outcome assessment at 1 month; the data collected in patients who cannot consent within that time frame are excluded from the study, as well as those for caregivers. This approach to recruiting patients is proving more effective than the initial approach.

In addition to this first challenge, our team experienced difficulty with delirium detection. In the research milieu, a delirium screening tool, the ICDSC, is administered three times a day as part of usual care for all post-surgical patients in the ICU, and as needed on the surgical ward. It was expected that delirious patients would be identified by a score of four or higher on the ICDSC, as recommended [19]. However, we observed that a number of patients with hypoactive delirium do not score four or more on the ICDSC. Hypoactive delirium is recognized by the scientific community as being highly underdiagnosed or misdiagnosed for depression because of its less behaviorally-disturbing nature [53, 54]. Until now, the most effective way to identify patients with hypoactive delirium has been to speak to all patients with a score of at least one on the ICDSC scale, and focus on identifying more subtle symptoms such as inattention or mild hallucinations.

It has been established that delirium results in negative consequences for patients, leaving them with psycho-functional sequelae [5, 6, 10], as well as for families who report high anxiety [10] and for the health care system [55]. The search for new strategies for delirium prevention, management, and monitoring, eventually leading to better outcomes for all areas affected by this serious syndrome, is pressing. The proposed pilot study protocol will enable us to build a larger study with a sufficient number of participants to ensure adequate statistical power that can potentially add to the knowledge on delirium management and monitoring. Another potential important contribution of this pilot study is in the validation of cerebral oximetry with NIRS. This promising physiologic measure of cerebral perfusion could fill a gap in providing an objective indicator for early detection and continuous monitoring of delirium. Finally, this study is proposed to assess the feasibility and acceptability of the study design and intervention which could potentially add to the literature on pilot studies because it is based on the recent literature on this research strategy [45–48].

